#### Operational considerations

Randomization will be stratified by APHRODITE group to improve treatment balance and precision of subgroup estimates. Baseline characteristics will be presented by the treatment arm within each APHRODITE group, and subgroup-specific effect estimates will be included in the main results table.

### Efficacy

#### Primary efficacy analysis

The primary efficacy endpoint of the trial is the proportion of participants who achieve sperm availability suitable for ICSI at any time from randomization through Week 16. Success is defined as the presence of viable sperm obtained either through ejaculated semen or through micro-TESE. All sperm-availability determinations will be centrally reviewed and adjudicated by laboratory personnel who remain blinded to treatment allocation. The endpoint is evaluated under a treatment-policy framework, meaning all participants are analyzed according to their randomized group regardless of treatment adherence, procedures performed, or timing variations. This approach provides an unbiased estimate of the overall effectiveness of hormonal therapy compared with standard-of-care management.

#### Secondary efficacy endpoints

Micro-TESE sperm retrieval success rate (SSR) among those undergoing surgery.Need for surgical sperm retrieval (any micro-TESE performed by Week 16).Time to first sperm availability (ejaculation or micro-TESE), from randomization.Embryological outcomes: ICSI fertilization rate, blastulation rate, blastocyst quality, and top-1-quality blastocyst rate (per couple cycle).Reproductive outcomes: Clinical pregnancy and miscarriage rates per embryo transfer; live birth (exploratory).

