## Method and analysis

### Study objective

The primary objective of this multicenter randomized controlled trial is to determine whether physiologic gonadotropin-based hormonal optimization (hCG with FSH) increases the likelihood of obtaining sperm suitable for ICSI—either through ejaculated sperm or through micro-TESE—within 16 weeks in hypogonadal men with idiopathic NOA, compared with SOC management without hormonal therapy.

The secondary objective is to evaluate the impact of hormonal therapy on surgical sperm retrieval rates, need for surgery, embryologic outcomes (fertilization, blastulation, blastocyst quality), and reproductive outcomes including clinical pregnancy, miscarriage, and live birth, as well as to assess treatment safety.

We primarily hypothesize that gonadotropin-based hormonal optimization (hCG + FSH) will increase the proportion of men with idiopathic NOA who achieve sperm availability for ICSI—either through ejaculated sperm or through micro-TESE—by Week 16, compared with standard-of-care management.

Our secondary hypothesis is that hormonal therapy will reduce the need for micro-TESE compared with standard-of-care and improve surgical sperm retrieval rates among men undergoing micro-TESE.

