### Study design and methods

This multicenter, randomized, controlled, parallel-group superiority trial assigned men 1:1 to hormonal therapy or SOC. Eligible participants had idiopathic NOA, total testosterone <350 ng/dL on two fasting morning tests, and FSH ≥7.6 IU/L (APHRODITE Groups 3–4). Key exclusions included cryptorchidism, prior chemotherapy/radiation, genetic NOA (AZFa/complete AZFb deletions), prior micro-TESE within 12 months, recent gonadotropin use, uncontrolled endocrine disease, severe liver disease, polycythemia, active malignancy, inability to comply, and presence of untreated clinical varicocele requiring correction. Table 2 illustrates the summary of the study design.

**Table 2 T2:** Summary of study design.

Design	Multicenter, randomized, controlled, parallel-group superiority trial (1:1)
Population	Idiopathic NOA; hypogonadal (TT <350 ng/dL on two fasting morning tests); FSH ≥7.6 IU/L (APHRODITE Group 3: 7.6–12.0 IU/L; Group 4: >12.0 IU/L). Exclusions: cryptorchidism, chemo/radiation, genetic NOA (e.g., AZFa/complete AZFb), testicular trauma/torsion, postorchitis. prior micro-TESE within 12 months; recent gonadotropin therapy (<6 months); uncontrolled endocrine disease; active malignancy; severe liver disease; polycythemia (Hct > 50%); inability to comply. Varicocele ≥ Grade 3
Interventions	Arm A: hCG + FSH therapy with monthly hormone-driven titration (hCG initial ∼83 µg SC twice weekly; no preset min/max; target TT >350–900 ng/dL) + FSH 150 IU SC twice weekly (increase to 150 IU SC three times weekly if ‘FSH reset’ < 1.5 IU/L); allow anastrozole 1 mg PO daily/letrozole 2.5 mg half-tablet alternate day if T/E < 10. Arm B: Standard-of-care (SOC) no gonadotropins
Follow-up	Participants in both arms will be followed up from randomization through Week 16 for ascertaining the primary composite endpoint. The SOC arm may undergo micro-TESE at any time within this window per standard scheduling; a semen analysis will be performed on the day of surgery to capture rare ejaculated sperm. The hormonal arm will undergo semen analyses at Weeks 12 and 16, with micro-TESE at Week 16 if ejaculated sperm is absent. No artificial delay is imposed on the SOC arm
Primary outcome	Success is defined as sperm available for ICSI at any time from randomization through Week 16 via ejaculation or micro-TESE, centrally adjudicated, and blinded to allocation

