### Interim analysis and sample estimation

A single planned interim review will be conducted after approximately 50% of participants have been randomized and have completed at least 12 weeks of follow-up. Because the primary endpoint incorporates sperm availability assessed up to Week 16, including micro-TESE outcomes, formal early efficacy or futility analyses based on conditional power were considered inappropriate and were therefore not planned.

Accordingly, the interim review will focus exclusively on
participant safety,protocol adherence, anddata completeness and trial conduct.No formal hypothesis testing for efficacy or futility will be performed during the interim review, and no alpha spending is planned.

In addition, a blinded sample size re-estimation (BSSR) will be performed once at least 30% of participants have completed Week-16 outcome assessment. The re-estimation will be based exclusively on the pooled overall event rate for the primary composite endpoint, without unblinding treatment allocation. Any increase in total sample size will be capped at 20% of the originally planned enrollment.

Missing primary endpoint data will be conservatively imputed as treatment failures regardless of reason, consistent with the treatment-policy estimand framework.

Supportive analyses for secondary outcomes will use multiple imputation under the missing-at-random assumption, incorporating treatment arm, study site, APHRODITE group, age, BMI, baseline hormonal profile, testicular volume, and interim semen findings. Sensitivity analyses using delta-adjusted missing-not-at-random assumptions will also be performed.

For adverse events and serious adverse events, missing data will be treated as absence of an event unless contradicted by site monitoring or Data Safety and Monitoring System (DSMB) review.

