## Discussion

### Generalizability

The results of this trial can be applied to a wide range of men with idiopathic non-obstructive azoospermia who also have low testosterone and elevated FSH, as these features are commonly seen in daily infertility practice. By including participants from multiple centers and using criteria that reflect real-world presentations, this study captures a representative group of patients. The standardized protocol for hormonal treatment, semen testing, and surgical procedures further strengthens the ability to apply the findings to similar clinical settings where male infertility is managed.

The difference in procedural timing between study arms reflects the pragmatic nature of the trial design. The control arm follows standard clinical practice without delaying indicated surgery, whereas the intervention arm incorporates a predefined hormonal optimization period intended to encompass approximately one spermatogenic cycle before surgical sperm retrieval is considered.

The composite primary endpoint was intentionally designed to reflect a pragmatic and patient-centered treatment goal: achieving sperm availability for ICSI irrespective of whether sperm is obtained from ejaculation or surgery. Although these represent distinct clinical pathways, both outcomes are biologically linked to spermatogenic recovery and are clinically meaningful to couples pursuing assisted reproduction. Importantly, the protocol prospectively separates micro-TESE avoidance and surgical sperm retrieval success as secondary endpoints to allow clinically interpretable assessment of these distinct components.

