## Estimands (ICH E9[R1])

Primary estimand (treatment-policy):
Treatment conditions: Arm A = hCG + FSH regimen with monthly hormone-guided titration (FSH fixed 150 IU 2×/week; increase to 150 IU 3×/week if “FSH reset” < 1.5 IU/L); Arm B = standard care (no gonadotropins).Population: All randomized idiopathic NOA participants meeting eligibility (TT < 350 ng/dL on two fasting mornings; FSH ≥ 7.6 IU/L; APHRODITE Groups 3 or 4).Variable (endpoint): Sperm available for ICSI by 16 weeks—success if sperm is present in ejaculate at Week 12 or 16, or (if ejaculate is negative) sperm retrieved at micro-TESE at Week 16.Intercurrent events strategy: Treatment-policy—outcomes counted regardless of adherence or pathway (e.g., early stop, skipping micro-TESE after ejaculate success, elective early micro-TESE at 12 weeks). Missing primary outcomes are treated as failure in the primary analysis, with supportive hypothetical analyses.Summary measure: Proportion with success by 16 weeks; between-arm comparison via risk ratio and risk difference with 95% CIs using a mixed-effects model (fixed: arm, APHRODITE group; random: site).Supportive estimands:
Hypothetical estimand: “What would the outcomes be if all participants completed week-16 assessments?”—analyzed using multiple imputation under MAR with delta-based MNAR sensitivity.Per-protocol estimand: Effect among participants without major protocol deviations (e.g., prohibited concomitants, major non-adherence, early elective micro-TESE without week-16 assessment).

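### The need-for-surgery endpoint records micro-TESE performed by Week 16, so an operation declined, postponed or never done counts as surgery avoided, and Arm A's surgery falls due just as the window closes

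*Protocol article*

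**What the plan says.** Secondary efficacy endpoints defines the variable as "Need for surgical sperm retrieval (any micro-TESE performed by Week 16". Study objective attaches a directional hypothesis to it: "hormonal therapy will reduce the need for micro-TESE compared with standard-of-care". The Discussion (Generalizability) relies on it for interpretation, stating that "the protocol prospectively separates micro-TESE avoidance and surgical sperm retrieval success as secondary endpoints", and Expected impact anticipates a decreased need for surgery if the intervention works.

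The timing of surgery differs by arm. For Arm A, Table 2 states: "The hormonal arm will undergo semen analyses at Weeks 12 and 16, with micro-TESE at Week 16 if ejaculated sperm is absent". The primary estimand says the same: "or (if ejaculate is negative) sperm retrieved at micro-TESE at Week 16". Table 3 marks micro-TESE at Week 16 only. For the control arm, Table 2 states: "The SOC arm may undergo micro-TESE at any time within this window per standard scheduling". Follow-up closes at Week 16 in both arms.

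**The concern.** The hypothesis is about need; the variable is about performance. The two agree only if every man who still lacks usable ejaculated sperm is operated on inside the window. In Arm A the operation depends on a negative Week-16 ejaculate and is due when the window shuts. In SOC there are up to 16 weeks in which to fit it. The definition does not separate a man who was not operated on because sperm was found from one who declined, was postponed or was lost to surgery. Both score as no surgery.

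No rule in the article repairs this:

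- The failure rule covers the primary endpoint only: "Missing primary endpoint data will be conservatively imputed as treatment failures regardless of reason".
- Inverse-probability weighting for differential surgical uptake (Sensitivity analyses) is specified for the micro-TESE retrieval rate only.
- Multiple imputation for secondary outcomes does not apply, because an operation that did not take place is an observed value, not a missing one.

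Limitations concedes that the lack of blinding may affect when micro-TESE is done. At stake is the surgery-sparing claim: postponement or refusal could be read as avoidance.

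**Working it through.** **Inputs from the article.** 430 per arm, 1:1, two-sided 5% level, secondary endpoints reported with 95% CIs. No rate or sample size is given for need for surgery. The article's only sample-size figure belongs to the primary endpoint, and it reproduces: (1.96 + 0.84)² × (0.45 × 0.55 + 0.55 × 0.45) / 0.10² = 7.84 × 0.495 / 0.01 = 388.08, and 388 × 1.1 = 427, planned as 430.

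**Assumed inputs.** Let e be the share of men with ICSI-suitable ejaculated sperm and no operation, set equal in both arms so that there is no treatment effect. Let s_A and s_S be the shares of the remaining men not operated on by Week 16 in Arm A and SOC. The article gives none of these, so a range is shown.

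**Formulas.** Proportion operated on: p = (1 − e)(1 − s). Difference: D = p_A − p_S = −(1 − e)(s_A − s_S). Standard error: √[p_A(1 − p_A)/430 + p_S(1 − p_S)/430]. The last column is the probability that the 95% CI lies wholly below zero, that is, falsely shows less surgery in Arm A.

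| e | s_A | s_S | D (points) | size of z | P(CI below 0) |
|---|---|---|---|---|---|
| 0 | 10% | 0% | −10.0 | 6.9 | >99% |
| 0 | 10% | 5% | −5.0 | 2.8 | 80% |
| 0 | 15% | 10% | −5.0 | 2.2 | 60% |
| 5% | 10% | 5% | −4.75 | 2.1 | 57% |
| 0 | 10% | 10% | 0 | 0 | 2.5% |
| 0 | 5% | 10% | +5.0 | 2.8 (reversed) | about 0 |

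Two rows written out:

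- 90% versus 95%: SE = √[(0.9 × 0.1 + 0.95 × 0.05)/430] = √(0.1375/430) = 0.0179, and 0.05/0.0179 = 2.8.
- 90% versus 100%: SE = √(0.09/430) = 0.0145, and 0.10/0.0145 = 6.9.

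**Smallest excess that matters.** With no treatment effect, the number of extra unperformed Arm A operations that puts the Wald 95% CI below zero is 15 men (3.5 points) if about 95% of SOC are operated on, 19 (4.4 points) at 90% and 25 (5.8 points) at 80%. If every SOC man is operated on it is 4 (0.9 points), but the Wald interval is unreliable at 4 versus 0, so that figure is rough.

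**Same scenarios under a needs-based count.** If surgery is avoided only when ICSI-suitable ejaculated sperm is documented and no micro-TESE was done, then with e = 0 the avoided proportion is 0% in both arms whatever s_A and s_S are. The false difference disappears, provided ejaculated sperm is looked for comparably in both arms.

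**The case against.** The strongest reply is that the direction is not established. SOC surgery is permitted, not required, and the article does not say how fast standard scheduling is. SOC men who wait, defer or decline also score as no surgery, which works against Arm A. This stands: the last row of the table is as consistent with the text as the first.

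Second, the full protocol or analysis plan may define a visit window around Week 16. That could rescue operations a few days late. It would not help with men who decline or are never operated on, so the definitional fault remains.

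Third, a reader might infer that the trial could confirm its secondary hypothesis by postponement alone. The article does not support that. Secondary endpoints carry 95% CIs without formal alpha. The hypothesis also has a retrieval-rate half that this mechanism does not touch. Elective Arm A surgery at Week 12 is foreseen as a deviation and would count as surgery. The primary composite, reported alongside, would move the other way, since an operation not done is a failure there.

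Fourth, a reader might also infer a serious loss of power for the primary endpoint from the same slips. That goes too far. Scoring missing outcomes as failures is a declared conservative choice, backed by a hypothetical estimand and tipping-point analyses. Any calculation that applies slippage to every success treats them all as surgical, although ejaculated successes need no operation.

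Finally, a needs-based definition can bring its own bias. Table 2 and Follow-up give SOC a semen analysis only on the day of surgery, against Weeks 12 and 16 in Arm A, so an SOC man not operated on may have no post-baseline semen result. This stands and is carried into the fix.

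**Conclusion.** The point holds as a mismatch between the concept named and the variable recorded. Non-performance counts as avoidance, and no stated rule corrects it. Its size depends wholly on the difference in unperformed operations between arms, which the article does not give. At 430 per arm, a 5-point excess in Arm A (10% versus 5%) yields a false 5-point reduction with z = 2.8, and 10% versus 0% yields 10 points with z = 6.9, both assuming no ejaculated sperm in either arm. Equal shares give no bias, and an SOC excess reverses it. The schedule makes an Arm A excess plausible but does not prove it. The conclusion is confined to the need-for-surgery endpoint and how it is read; it calls for no change to the primary endpoint or its Week-16 landmark.

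**What to change.** In Secondary efficacy endpoints, count surgery as avoided only when ICSI-suitable ejaculated sperm is documented by Week 16 and no micro-TESE was done. Report micro-TESE performed, postponed and declined as separate rows by arm, and do not present non-performance as the avoidance described under Generalizability.

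Reconcile the semen-testing passages. Table 2 and Follow-up give SOC a test only on the day of surgery, while Table 3 lists Weeks 12 and 16 without naming an arm. The text should make ascertainment of ejaculated sperm comparable in both arms, or state the remaining difference in the number of looks as a limitation of this endpoint.

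The cost is small: endpoint wording, some extra tabulation with reasons for non-performance, and probably a smaller apparent reduction in surgery. If semen testing is aligned between arms, additional SOC samples may be needed. The timing of surgery need not change.

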#### Efficacy analysis

**Primary analysis:** Compare proportions at Week 16 between arms using a risk difference and risk ratio with 95% CIs (Wald/Newcombe). The primary efficacy analysis will use a mixed-effects generalized linear model including a treatment arm and the APHRODITE group as fixed effects and the study site as a random intercept to account for clustering by center. A log-binomial mixed model will be preferred for estimating adjusted risk ratios. If convergence issues occur, a modified Poisson mixed-effects model with robust variance will be used as a prespecified alternative. The modified Poisson approach is specified solely as a fallback method in the event of log-binomial model non-convergence and does not represent a separate primary analytical method.**Sensitivity analyses:**
•**Time**-**to**-**event** (Cox model; log-rank) for time to first sperm availability.•**Per**-**protocol** analysis excluding major deviations.•**Tipping**-**point** analyses for missing outcomes.**Subgroups (prespecified):** APHRODITE Group 3 vs. 4, site, baseline TT strata (<250 vs. 250–349 ng/dL), age (<35 vs. ≥35), varicocele grade (<3 vs. 3). Interaction terms to assess heterogeneity.**Multiplicity:** Secondary endpoints reported with 95% CIs; no formal alpha allocation unless specified in a hierarchical plan.**Handling intercurrent events:** Treatment policy (analyze as randomized). For couples without ART attempts by Week 16, embryologic/reproductive endpoints treated as not evaluable; no imputation for primary endpoint beyond the landmark rule.

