## Introduction

Non-obstructive azoospermia (NOA) represents the most severe form of male infertility and affects approximately 10%–15% of infertile men (1). In men with idiopathic NOA, impaired intratesticular testosterone production and elevated follicle-stimulating hormone (FSH) levels often reflect underlying Sertoli cell dysfunction and reduced spermatogenic capacity (2). Currently, microdissection testicular sperm extraction (micro-TESE) remains the preferred method of sperm retrieval in these patients, offering the highest likelihood of obtaining sperm for intracytoplasmic sperm injection (ICSI). However, sperm retrieval success rates remain highly variable, generally ranging from 40% to 60%, and many men undergo invasive surgery without successful sperm recovery (3, 4).

Despite extensive investigation, reliable preoperative predictors of sperm retrieval remain inconsistent across studies and populations. Several clinical, hormonal, and molecular biomarkers have been explored, including FSH, inhibin B, anti-Müllerian hormone, and testicular histopathology, but no single marker has demonstrated sufficient predictive accuracy for routine clinical use. Representative studies evaluating biomarkers and predictors of sperm retrieval success in idiopathic NOA are summarized in Table 1.

**Table 1 T1:** Clinical studies involving predictors/biomarkers for sperm retrieval in idiopathic NOA and related micro-TESE outcomes.

Year	Reference	N	Population	Sample type	BM(s)	Threshold (cutoff)	Sens	Spec
2023	Deng et al. (14)	168	Idiopathic NOA undergoing micro-TESE	Serum	INHB; AMH; INHB/AMH	INHB 21.51 pg/mL; INHB/AMH 3.19	86.3% (INHB/AMH)	53.8% (INHB/AMH)
2021	Zarezadeh et al.(17)	—	NOA (predictors review)	Serum/seminal (review)	FSH, LH, TT, INHB, AMH, E2, PRL, leptin (various)	Heterogeneous; no unified cutoffs	—	—
2021	Majzoub et al. (with S.C. Esteves) (16)	297	NOA; staged Testicular Sperm Aspiration (TESA) → micro-TESE	Clinical/serum	Multivariable model (age, testis size, FSH, etc.)	Model-based (no single threshold)	NR	NR
2021	Shiraishi et al. (18)	76	NOA vs. OA; subset on anastrozole	Testicular fluid/serum/tissue	Intratesticular T and E2, aromatase expression	No diagnostic cutoff; mechanistic	—	—
2023	Shi et al. (15)	114	Idiopathic NOA, micro-TESE	Testicular tissue	circ_MGLL (circRNA) + clinical nomogram	Nomogram (probability-based)	-	-

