#### Statistical model and test of interaction

The analysis will be interaction-driven. Treatment effects within subgroups will be descriptive unless the treatment-by-subgroup interaction is statistically significant.

A generalized linear model (identity link, robust standard errors) shown in Equation 1 will be used:$$Y\_i\;=\beta_{0\;}+\beta_{1}\cdot \mathrm{Treatment}\_i+\beta_{2}\cdot \mathrm{Group}\;4\_i+\beta_{3}\cdot (\mathrm{Treatment}\_i\times \mathrm{Group}\;4\_i)+\gamma^{T}X\_i+u\_\mathrm{site}+\varepsilon \_i,$$(1)where Y_i represents the binary composite outcome (sperm available for ICSI by Week 16), Group 4_i is an indicator variable for APHRODITE Group 4, and X_i denotes prespecified covariates (female age, male age, center, baseline semen parameters, baseline TT/E2, baseline DNA Fragmentation Index (DFI), and number of Metaphase II (MII)). The interaction term *β*_3_ tests for a differential treatment effect between Groups 3 and 4. Random intercepts for site will account for clustering, and results will be presented as marginal risk differences.

The test for interaction will use a two-sided *α* = 0.05. Although prospectively specified and biologically motivated, subgroup analyses are considered supportive and hypothesis-generating unless sufficiently large interaction effects are observed. The trial is primarily powered for the overall treatment effect rather than formal interaction testing. The Table 3 illustrates SPIRIT schedule for enrollment, intervention, and assessments.

**Table 3 T3:** SPIRIT schedule of enrollment, interventions, and assessments.

Procedure/time point	Enrollment (≤28 days)	Baseline (W0)	W12	W16
Eligibility and consent	X			
Randomization		X		
hCG + FSH (Arm A)		X	X	X
Endocrine labs (TT, E2, LH, FSH; CBC/Hct, LFTs, lipids)		X	X	X
Semen analysis		X	X	X
Micro-TESE (if needed)				X
AE/SAE assessment		X	X	X

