#### Reporting and visualization

Forest plots will display risk differences (treatment − control) with 95% confidence intervals for the overall population and for each subgroup. The interaction *p*-value will accompany the forest plot. A Supplementary Figure will show treatment effect as a function of continuous FSH modeled with restricted cubic splines (three to four knots) and 95% confidence bands.

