#### Randomization and masking

Randomization: Central web platform; 1:1 allocation; stratified by site and APHRODITE group (3 and 4); variable block sizes; concealed via pharmacy/Clinical Research coordinator (CRC)-controlled access.

Masking: Surgeons/participants unblinded; laboratory personnel and central adjudicators blinded. Embryologists adjudicate outcomes using deidentified labels.

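### The primary model is valid but leaves out baseline age, testosterone, continuous FSH and testicular volume, forgoing a small, nearly free gain in precision

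*Protocol article*

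**What the plan says.** The Efficacy analysis section describes the primary model as a "mixed-effects generalized linear model including a treatment arm and the APHRODITE group as fixed effects and the study site as a random intercept". The summary measure in the Estimands section agrees: "mixed-effects model (fixed: arm, APHRODITE group; random: site". Randomization is "stratified by site and APHRODITE group (3 and 4", so the model holds exactly the stratification factors. FSH enters through APHRODITE group alone, as a split at 12.0 IU/L.

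Other parts of the protocol article use more baseline information:

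- Multiple imputation for secondary outcomes works by "incorporating treatment arm, study site, APHRODITE group, age, BMI, baseline hormonal profile, testicular volume, and interim semen findings" (Interim analysis and sample estimation).
- The interaction model, Equation 1, adjusts for "prespecified covariates (female age, male age, center, baseline semen parameters, baseline TT/E2, baseline DNA Fragmentation Index (DFI), and number of Metaphase II (MII".
- Table 3 marks "Endocrine labs (TT, E2, LH, FSH; CBC/Hct, LFTs, lipids" at baseline, and eligibility itself requires two testosterone results and an FSH value (Population).
- Table 1 cites a retrieval study that used a "Multivariable model (age, testis size, FSH, etc".

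The Reporting and visualization section plans one forest plot of risk differences "for the overall population and for each subgroup". It does not say which model supplies the overall row.

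**The concern.** Covariates that predict the outcome reduce the variance of the treatment estimate, even when randomization is sound. The plan treats age, hormones and testicular volume as informative enough to impute secondary outcomes, and age and testosterone/estradiol as worth adjusting for in the interaction test, yet leaves them out of the comparison that decides the trial. The Sample size estimation section speaks of 80%–90% power, but the calculation under Power considerations uses 80%, so extra precision would be useful.

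The second issue is consistency. The primary model prefers a log-binomial form with two factors; Equation 1 uses an identity link with a longer list. If the overall row of the forest plot comes from the primary model, it would rest on a different adjustment set from the subgroup rows beside it.

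**Working it through.** **1. The plan's own figure.** Inputs from Power considerations: 40% vs 50%, two-sided alpha 0.05, power 80%, dropout 10%.

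n per arm = (1.96 + 0.84)² × (0.45×0.55 + 0.55×0.45) / 0.10² = 7.84 × 0.495 / 0.01 = 388.08, so 388 as stated. With 430 planned per arm and 10% lost, 430 × 0.9 = 387 are evaluable.

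Power = Φ{[0.10√n − 1.96√(2×0.45×0.55)] / √(0.40×0.60 + 0.50×0.50)}. At n = 387 this is Φ{(1.967 − 1.379)/0.700} = Φ(0.840) = 80.0%. The planned power therefore needs no covariates.

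**2. Effect of adding covariates.** Let R² be the share of outcome variance that the added covariates explain *beyond* APHRODITE group and site. The documents give no value, so a range is assumed. Variance scales by (1 − R²), so the effective sample per arm is 387/(1 − R²), and the equivalent number of extra men is 774/(1 − R²) − 774.

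| Residual R² (assumed) | Effective n per arm | Power | Equivalent extra men |
|---|---|---|---|
| 0 | 387 | 80.0% | 0 |
| 0.02 | 395 | 80.8% | 16 |
| 0.05 | 407 | 82.0% | 41 |
| 0.10 | 430 | 84.0% | 86 |

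For the confidence interval, the unadjusted half-width is 1.96√(0.49/387) = 7.0 points. Multiplying by √(1 − R²) gives 6.9 points at R² = 0.02 and 6.6 at R² = 0.10.

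To put the range in context, on a binormal approximation at a 45% event rate a baseline score with AUC 0.60, 0.65 or 0.70 corresponds to R² of about 0.03, 0.07 or 0.12.

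**3. Simulation check.** 3,000 trials per setting, 387 per arm, 40% vs 50%, one baseline prognostic score. Monte Carlo standard error is about √(0.8×0.2/3000) = 0.7 points.

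- Logistic standardisation against an unadjusted test: 78.8% to 80.0% (R² 0.02), 79.4% to 81.9% (0.05), 79.9% to 84.1% (0.10).
- Robust modified Poisson without and with the score: 80.0% to 81.4%, 78.2% to 81.5% and 79.4% to 84.7% for log-odds slopes of 0.36, 0.55 and 0.77 per SD. The average risk ratio was 1.25 both ways, so the omission causes no bias.

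**4. If missing outcomes are counted as failures.** The plan's rule keeps all 430 per arm in the analysis. With 10% missing in each arm the rates become 0.9×40% = 36% and 0.9×50% = 45%. Power is then 76.8% without added covariates, and 77.6%, 78.9% or 81.0% at R² of 0.02, 0.05 or 0.10. The gain is again about 1 to 4 points.

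**5. Which variables are available.** Testosterone and FSH must be known before entry. Male age is in Equation 1, and age is also a planned subgroup factor. Testicular volume is different: among the trial's own variables it appears only in the imputation list, not in Table 3 or Equation 1, so its recording at baseline has to be confirmed.

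**The case against.** The strongest reply is that nothing here is wrong. Adjusting for the stratification factors alone is a standard, prespecified choice, and the two places that state the primary model agree. The sample size was built on unadjusted proportions and counts on no gain from covariates. That stands.

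The size of the gain is also open. The Introduction calls predictors of retrieval inconsistent across studies and finds no single marker accurate enough for routine use. The cited model with age, testis size and FSH comes from a different NOA population and reports neither sensitivity nor specificity. Restricting entry to low testosterone and raised FSH may further narrow what those values can explain, and group and site already take up part of it. This argues for the lower part of the range. It does not remove the point: a covariate can be too weak to guide patient selection and still reduce variance jointly with others.

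The forest-plot argument is conditional, because the text leaves the source of the overall row open. Both the overall and subgroup results are meant as risk differences, and different baseline adjustment does not in itself change the marginal quantity being estimated. The subgroup analysis is also labelled supportive.

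Finally, log-binomial models can fail to converge once continuous covariates are added. The plan already names modified Poisson with robust variance as the fallback, so this is no separate defect.

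**Conclusion.** This is an efficiency and consistency point. The primary model forgoes a gain of about 1 to 4 percentage points of power, or an interval about 1% to 5% narrower, provided the omitted covariates explain 2% to 10% of outcome variance beyond APHRODITE group and site. That provision is an assumption which the documents neither supply nor rule out.

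A reader might infer three stronger things, none of which the documents support:

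- **That the trial falls short of its planned power because of the model.** It does not: 388 per arm and 80% reproduce with no covariates. The drop to 76.8% in step 4 comes from the missing-data rule, a separate matter.
- **That chance imbalance in age or testicular volume biases the result.** Chance imbalance is ordinary sampling error, which the confidence interval covers; the simulated risk ratio was unchanged by adjustment.
- **That hormone values are ignored.** FSH is present but coarsened to two levels. What is missing is continuous FSH and total testosterone.

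**What to change.** In the Efficacy analysis and Estimands sections, add a short, prespecified list of true baseline covariates to arm, APHRODITE group and site: male age, continuous or log FSH, total testosterone, and testicular volume if it is recorded at baseline. Report the marginal risk difference and risk ratio with 95% CIs. Two routes would serve: standardisation over all randomized men from a logistic model that keeps site, or adding the covariates to the robust modified Poisson model already named. Keep the present model as a sensitivity analysis.

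Use the same list in Equation 1 and state which model supplies the overall row of the forest plot, so that all rows share one adjustment set. Do not carry the present Equation 1 list into the primary model. The MII count arises in the partner's treatment cycle and exists only for couples who reach it, so it should be dropped. Baseline semen parameters and DFI say little or nothing in azoospermic men, and testicular volume is not on that list.

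The cost is protocol or SAP wording, a little programming and a simple imputation rule for missing baseline values that ignores arm and outcome. Testosterone and FSH should rarely be missing, since eligibility depends on them. No additional patients are needed. The list must be fixed before treatment allocation is unblinded.
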